## Abstract

**Background:**

Zambia is struggling to meet the 95-95-95 targets established by the Joint United Nations Programme on HIV/AIDS for adolescent girls and young women (AGYW), and HIV incidence remains high. The Zambian government has declared adolescent HIV prevention and sexual health as priorities, but new strategies are needed to facilitate HIV testing uptake among AGYW. Mother figures (MF), who are the center of Zambian families, may hold the key. The excessive burden on the healthcare workforce has impeded the implementation of effective HIV prevention programs. To sustain effective programs, implementation strategies are needed that reduce worker burnout and improve job satisfaction and employee retention. Task shifting to peer leader intervention delivery and attention to healthcare worker stress has the potential to strengthen and sustain program delivery. This study will test an intervention called ZAIMARA for AGYW and MF to improve HIV testing uptake and evaluate implementation outcomes when delivered by peer leaders.

**Methods:**

This 2-arm individually randomized hybrid effectiveness-implementation trial will compare ZAIMARA to a health promotion (HP) program across five sites in Lusaka. We will enroll up to 650 dyads comprised of 15-19-year-old Zambian AGYW and their MF. Peer leaders randomized and trained to deliver ZAIMARA or HP will receive mental health distress screening and referral versus nutrition and exercise screening. AGYW-MF dyads will participate in a 2-day group workshop and complete 6-, 12-, 18-, and 24-month assessments. Peer leaders will complete 6- and 12-month assessments. Primary outcomes are HIV-testing uptake for AGYW and job retention for peer leaders at 6-months. Secondary outcomes include incident sexually transmitted infections, including HIV, uptake of pre-exposure prophylaxis, and safer sexual behavior at 12-, 18-, and 24-months. We will evaluate implementation outcomes and intervention costs.

**Discussion:**

This study is poised to add a novel approach to HIV prevention among AGYW in Zambia and inform implementation considerations. ZAIMARA may provide a scalable solution to improve HIV testing and prevention practices for AGYW and identify features of implementation that strengthen sustainability. Findings will inform national HIV prevention strategies in Zambia and offer insights into the broader application of family-based interventions in similar low-resource settings globally.

**Trial registration:**

ClinicalTrials.gov, NCT06503666, Registered on 10 July 2024.

## Background

Zambia is unlikely to meet the 95-95-95 targets established by the Joint United Nations Programme on HIV/AIDS (UNAIDS) for adolescent girls and young women (AGYW) by 2030 [1]. HIV prevalence among 15–19 year-olds is 3.3%, with increasing incidence from 2010 to 2020 among AGYW [2]. Females are four times more likely to acquire HIV than their male peers (8.6% vs. 2.1%), AGYW HIV testing rates are low (45.4%), and 71.2% do not know their status. Of particular concern, over 63% of AGYW reported sexual activity, but only 37.1% used a condom at last sex [1–3]. Sexually transmitted infections (STIs) are a marker of risk for HIV, because they reflect unprotected sexual activity. The prevalence of STIs in Zambia is unknown because treatment is syndromic, and most STIs are asymptomatic. Thus, many STIs go untreated risking potentially serious reproductive health consequences, like infertility. Despite available public health services, including free HIV testing, prevention, care, and treatment, uptake remains suboptimal [4]. As a consequence, the Zambian government has declared adolescent HIV prevention and sexual health as key goals in its national strategy [5].

Unfortunately, barriers to HIV prevention, including cultural factors that discourage effective use of sexual and reproductive health services (SRH) in Zambia impede uptake [6]. AGYW may have fears and misconceptions of HIV and experience stigma surrounding adolescent sexuality. Anxiety can lead to a lack of social support from partners and peer groups that would otherwise be protective [7]. Families and communities are often the source of perceived stigma and reinforce inequitable gender and social norms that amplify girls’ vulnerability [6]. Similarly, health systems are frequently inaccessible and unfriendly to young people [8]. These intersecting barriers deter access to HIV and SRH services and long-term engagement in care.

As new HIV infections continue to outpace viral suppression, primary prevention remains the most viable strategy to stem the epidemic among Zambian AGYW. Yet, the effects of psychosocial interventions traditionally focused solely on adolescent behavior have been disappointing or relatively short-lived [9]. By contrast, programs that actively engage trusted family members in HIV prevention efforts may produce stronger and longer-lasting impacts, because they can address the sociocultural and structural drivers of HIV and challenge gender dynamics and HIV stigma in a safe and culturally appropriate venue [10–13]. In particular, mothers and other important female caregivers (aunts, cousins) (hereafter referred to as “mother figures” or MF) play a central role in AGYW’s sexual development and decision-making [14–18], and they can be role models for healthy relationships, open-communication, and self-care [19–24]. AGYW want to learn about sex from responsible adults, and mother figures can communicate prevention messages over time and tailor them to AGYW’s developmental stage. Family-based HIV prevention interventions can help AGYW and MF rethink gender roles and stereotypes [25], and MF may be a catalyst to promote AGYW safer sexual behavior, HIV testing, and PrEP uptake [25–27]. Hence, involving MF adds a new tool to the HIV prevention toolkit and can potentially improve the feasibility and acceptability of HIV testing and PrEP uptake.

Evidence for the effectiveness of family-based HIV prevention is growing. Programs that improve the quality of mother-daughter conversations about sexual decision-making, teach parents to use accurate and unambiguous information, and challenge cultural taboos that are barriers to mother-daughter communication about sex [10] can increase AGYW’s prevention behavior. Group-delivered family-based interventions can build on the power of collective and community support, change social and cultural norms to favor HIV prevention uptake, and create a sense of unity and collective efficacy to stem HIV infections among AGYW [28–30]. Yet, uptake and testing of family-based HIV prevention in Zambia has been slow, in part because involving adult family members in AGYW sexual health promotion challenges traditional values about adolescent pre-marital sexual behavior [31].

This study will adapt and evaluate *I*nformed *M*otivated *A*ware and *R*esponsible *A*dolescents and Adults (IMARA) for Zambian AGYW and their MF. IMARA was originally developed and tested in the United States with Black/African American 14–18-year-old AGYW and their primary female caregiver. A group randomized controlled trial in the U.S. showed reduced STI incidence among AGYW who received IMARA at 12-month follow-up compared to a matched control group [32], earning it the designation as a CDC “best evidence” HIV-prevention intervention. In 2019, we adapted IMARA for the South African context (IMARA SA), and findings from a pilot study revealed decreased AGYW mental distress [33], strong intervention feasibility, acceptability, and fidelity, and positive trends for increased South African AGYW’s HIV testing, PrEP uptake, and sexual risk reduction [34]. From 2022 to 2025, we systematically adapted IMARA for Zambia (i.e., *ZA*mbian *I*nformed *M*otivated *A*ware and *R*esponsible *A*dolescents and *A*dults; ZAIMARA) and carefully documented adaptations [35].

During the adaptation process, we recorded implementation determinants and processes informed by the Exploration, Preparation, Implementation, Sustainment (EPIS) Framework [36–39]. We identified a critical barrier to program sustainability, namely low staff retention. Like most resource-constrained settings, the Zambian healthcare workforce is overtaxed and understaffed. They report mental distress, emotional strain, and workplace burnout due to excess psychosocial demands [40]. Many healthcare workers leave their jobs prematurely due to low satisfaction, inadequate training, and feeling devalued, resulting in high costs for retraining and program continuity. To address this, we will use two implementation strategies, task shifting and mental health screening with referral, to reduce health worker burden and improve job retention. We will hire and train peer leaders to deliver ZAIMARA and evaluate the feasibility, acceptability, and fidelity of this alternative workforce. Research indicates that peer leaders can be trained to carry out a range of healthcare tasks [41–43] and deliver evidence-based interventions with fidelity with proper supervision [43]. We will also randomly assign peer leaders to receive monthly mental health screening and referral (where relevant) versus monthly nutrition and exercise screening and assess job retention at 6-months post-intervention.

## Overall study objectives

This study is a 2-arm hybrid effectiveness-implementation trial conducted in three phases. In Phase 1, which is complete, we systematically adapted IMARA for the Zambian context [35]. In Phase 2, we will evaluate ZAIMARA’s effectiveness on AGYW HIV testing, HIV and STI incidence, PrEP uptake, and sexual behavior. We will also assess the impact of monthly mental health screening and referral on peer leader job retention. In Phase 3, we will evaluate the acceptability, appropriateness, feasibility, treatment fidelity, sustainability, and costs associated with ZAIMARA.

## Methods/design

Aim 1 (IMARA adaptation completed. See Sissoko et al., under review).

### Aim 2 effect of ZAIMARA on AGYW HIV testing uptake at 6-months

**Overview**. AGYW and MF will be recruited from five geographically distinct communities and randomly assigned to the experimental (ZAIMARA) or control (health promotion) arm as a dyad. They will complete surveys at baseline, 6-, 12-, 18-, and 24-month follow-up using computerized assisted self-interview technology (CASI). AGYW will provide urine for STI screening, and we will offer HIV testing and pre-exposure prophylaxis (PrEP) at each time point. AGYW will receive healthcare free of charge at the site clinic as needed, including STI treatment in line with national guidelines. ZAIMARA and HP workshops will be delivered over 2-days (~ 12 h) and matched in time and intensity. Day 1 will last approximately 6-hours and include eligibility screening, consent/assent, the baseline survey, randomization, workshop day 1, and clinical assessments (HIV and STI testing, PrEP uptake). AGYW and MF will return to the site on a separate occasion (approx. 1 week later) for workshop day 2 of the intervention (~ 8 h). Sessions are conducted with AGYW and MF together and separately. To enhance the workshop experience and ensure participants’ comfort, light snacks, lunch and beverages will be provided during both workshops.

**Study sites**. The study will be conducted in five geographically distinct catchment areas in Lusaka, each feeding into a Ministry of Health (MoH) district clinic or hospital. The sites were chosen based on the high volume of adolescents seeking SRH services and the surrounding community population of AGYW. We expect enrollment of at least 2–3 AGYW-MF dyads per day per site.

**Recruitment.** Research staff, with assistance from neighborhood health committee (NHC) members will recruit AGYW and MF. NHC members are well-known in the community and recognized by the MOH as responsible for mobilizing and sensitizing communities about cross-cutting health issues, including research studies. The project coordinator will train NHC members to deliver recruitment messages using the recruitment brochures, and they will accompany outreach sessions. Recruiters will establish a landmark location in the neighborhood from which they can easily approach (or be approached by) women and AGYW. NHC members will initiate contact with a potential participant (AGYW or MF) and ask if she would like more information about the project. If yes, the research staff will explain the study and screen for inclusion/exclusion criteria. In addition, NHC members and research staff will implement a systematic door-to-door sensitization and recruitment strategy. Specifically, they will visit every fourth household within each selected neighborhood. During these visits, they will provide information about the study, address any questions or concerns from potential participants, and conduct preliminary screening to assess eligibility for study enrollment.

We will enroll approximately 16–20 dyads twice per month at each site for one year, beginning with two sites and then adding the remaining three sites. NHC members will receive approximately 50 kwacha (approx. 2 USD) for each eligible AGYW referred to the study to cover associated text/call costs and 50 kwacha to cover transport costs.

**Participants**. We will enroll up to 650 AGYW-MF dyads (120–130 dyads per site) for a total of 1200 to 1300 individuals. AGYW will be 15–19 years-old, female sex assigned at birth, unmarried, reside within the study catchment area, speak IciNyanja, ChiBemba, or English or a combination (the primary regional languages), willing and able to provide consent (≥ 18 years old) and/or assent (< 18 years old), and not known to have HIV (i.e., no positive test and not on ART). AGYW who participated in study Phase 1 or are enrolled in another sexual health intervention at the research site will be excluded. AGYW may or may not be sexually active; information about AGYW sexual activity will not be shared with MF. AGYW who test positive for HIV at baseline will complete the workshop, but then they will exit the study because it is not designed to provide support for persons with HIV. AGYW who become pregnant during the study may continue to participate.

MF are defined as an important and influential female in AGYW’s life (e.g., mother, aunt). MF will be chosen by the AGYW and agreed upon by the guardian/mother. MF must be ≥ 24-years-old, living with or in daily contact with the AGYW, speak IciNyanja, ChiBemba, or English or a combination, and willing and able to provide consent. MF who participated in study Phase 1 will be excluded.

**Consent/assent**. Study staff will explain research activities separately to MF and AGYW, allowing for independent consent and assent to prevent coercion. AGYW and MF must agree to participate as a dyad, but AGYW refusal will supersede MF consent. Consent/assent forms will explicitly state exceptions to confidentiality, for example, findings of suicidal ideation requiring referral, and these will be verbally reviewed with participants. The consent and assent documents will state that no information about AGYW sexual activity or HIV and STI test results will be shared with MF, reducing this barrier to consent/assent.

**Randomization**. We will randomize AGYW-MF dyads to one of two conditions (ZAIMARA or HP) following the baseline assessment (Fig. 1). We will use stratified permuted block randomization (blocks of 2) to ensure uniform distribution across arms and a balanced allocation (*n* = 300–325 ZAIMARA and *n* = 300–325 HP) throughout enrolment. AGYW and MF dyads will be randomized to the same condition. By stratifying the randomization process at the clinic level, we will account for potential variations in participant characteristics by neighborhood or clinic-specific factors, enhancing the validity and reliability of the study findings. Pre-determined randomization logs at each site will guide assignment to arms.

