***Individual factors***	
Knowledge about HIV, STI, PrEP, HIV testing and attitudes about PrEP	Facts of HIV/AIDS/STI/PrEP/HIV Testing; Prevalence and incidence for women; Perceived vulnerability; Personal risk triggers (people, places, feelings) and risk plans; Demonstrate and practice condom use; Importance of regular HIV testing and PrEP use where appropriate to risk behavior
Mental health	Destigmatize mental health; Links between mental health problems and HIV risk behavior; Recognize how feelings trigger risk-taking; Teach healthy coping strategies; Referrals for counseling

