***Structural factors***	
Gender dynamics	Expectations of women; Media images; Healthy and unhealthy relationships; Gender Based Violence; Gender role expectations and stereotypes; impact of gender of dynamics on HIV/STI risk
Partner relationships	Implications of age discrepant partners and concurrent partnerships; Importance of HIV testing, STI testing and treatment, and PrEP use and persistence; Communication with partners about HIV testing and PrEP
HIV stigma and discrimination	Changes in community norms to reduce stigma toward HIV/STIs, PrEP, and HIV testing

**Health promotion (HP): Time- and attention-matched control**. HP will be delivered as the comparison program and was used as the control group in IMARA SA. HP focuses on promoting healthy living by encouraging good nutrition, regular exercise, and informed consumer behavior. Although the HP curriculum does not explicitly address HIV/STI prevention, it includes basic information about HIV and other STIs due to the high-risk for AGYW. Like ZAIMARA, HP uses interactive games, videos, worksheets, and group discussion and MF and AGYW will meet in separate groups and together.

**Contamination**. Contamination across arms will be minimized as follows. (1) Peer leaders will not overlap, and training will occur separately. (2) ZAIMARA and HP will occupy different spaces at the site to reduce participant contact.

**Retention.** At baseline, we will obtain AGYW and MF phone numbers, home address (and draw a map), and other contact information (phone/text/WhatsApp). We will collect the phone numbers, home addresses, and text/WhatsApp information for at least two persons who will always know how to reach them in the future. We will make reminder calls the day before each workshop day and follow-up assessments to confirm attendance, and we will update our locator information at each contact. If the phone number/text/WhatsApp is disconnected, we will contact people from participants’ records. If AGYW were recruited through a clinic site (vs. outreach), we will seek assistance from the health facility and NHC members to locate them. Research assistants will visit the AGYW’s and MF’s last known address to try to locate them in-person. If the AGYW and/or MF no longer live at the address, we will ask their contacts to help us locate them. We will continue to try to locate them until the window for their assessment closes.

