**Study assessments.** AGYW and MF will complete 1.5-hour surveys via CASI at baseline, 6-, 12-, 18-, and 24-months post-intervention, and research staff will be present to answer questions and assist participants as needed. AGYW will provide a urine sample to test for three STIs (gonorrhea, chlamydia, and trichomoniasis). At the end of workshop day 1, AGYW will be offered HIV testing and PrEP (where appropriate). AGYW who want and are eligible for PrEP will receive a one-month supply or referral for PrEP depending on their preference and available supplies. They will also be referred to PrEP services closest to them for refills. AGYW may refuse HIV and STI testing and/or PrEP and remain in the study. AGYW and MF will each receive K200 (~$9.00) on both workshop days and each follow-up assessment, K200 for transport, and other incentives (e.g., T- shirts, sanitary towels, hygiene products such as soap at each visit) during in-person visits.

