### Statistical analysis

Preliminary analyses will summarize baseline characteristics of AGYW, MF, and peer leaders, generate frequencies (proportion) for categorical variables, medians (interquartile range) for continuous variables, and summary statistics of predictor, outcome, and mediating/moderating variables to screen and clean the data. We will evaluate randomization integrity by examining the distribution of baseline characteristics between randomization groups (i.e., AGYW assigned to ZAIMARA versus HP, peer leaders assigned to ZAIMARA versus HP, and peer leaders assigned to screening (mental health distress versus nutrition/exercise). We will adjust for potential confounders not balanced at baseline. We will examine if AGYW and peer leaders who complete the follow-up assessments differ systematically at baseline from those lost to follow-up. We will evaluate correlations among the variables, inspect scale reliabilities, and create summary scores. We will use models with random intercepts to account for clustering (if needed) and test the significance of clustering of subjects within groups and within sites.

**Aim 2**. The primary analysis will be based on the intention-to-treat population. We will use a two-sided z-test with unpooled variance to test the inequality of the proportion of HIV testing uptake at 6-months among AGYW who receive ZAIMARA compared to AGYW who receive HP. We will use log-binomial generalized linear model to estimate the effect of ZAIMARA on proportion with HIV testing uptake at 6-months, adjusting for potential confounders. Likelihood p-value < 0.05 will be considered statistically significant. We will evaluate the intervention effect on secondary *binary* outcomes (e.g., PrEP uptake, incident STI) in an analogous way. We will perform subgroup analyses, using test of interaction [78, 79] to evaluate if the effect of ZAIMARA on the primary outcome (HIV testing) differs systematically depending on hypothesized variable, such as mental health (e.g., depression, anxiety). We will include interactions between treatment condition and subgroup covariates in the generalized linear model, and obtain effect estimates, 95% confidence intervals, and p-values. For *continuous* secondary outcomes (e.g., HIV/STI knowledge score), we will evaluate the effect of ZAIMARA using linear regression models.

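### The first HIV test offer (and apparently the urine sample) comes after randomisation and workshop day 1, so HIV-positive exits and the known-negative baseline set may differ by arm

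*Protocol article*

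**What the plan says.** The Overview of Aim 2 gives the order of day 1 after screening and consent: "the baseline survey, randomization, workshop day 1, and clinical assessments (HIV and STI testing, PrEP uptake". The Study assessments paragraph of Aim 2 confirms it for HIV: "At the end of workshop day 1, AGYW will be offered HIV testing and PrEP (where appropriate". That paragraph does not say when on day 1 the urine sample is taken, so the timing of the STI sample rests on the list order in the Overview.

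The Randomization paragraph says: "We will randomize AGYW-MF dyads to one of two conditions (ZAIMARA or HP) following the baseline assessment". Read with the Overview, the baseline assessment that precedes randomisation is the survey, not the tests. The Participants paragraph requires only that a girl is not known to have HIV, and no HIV test before randomisation is described.

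Two rules then act on the result. Under Participants: "AGYW who test positive for HIV at baseline will complete the workshop, but then they will exit the study". Under Study assessments: "AGYW may refuse HIV and STI testing and/or PrEP and remain in the study".

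The arms differ in what they teach before the offer. Table 1 lists among ZAIMARA's activities: "Importance of regular HIV testing and PrEP use where appropriate to risk behavior". The control description begins: "Although the HP curriculum does not explicitly address HIV/STI prevention". It adds that basic HIV and STI information is included. The Statistical analysis section states for Aim 2: "The primary analysis will be based on the intention-to-treat population".

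**The concern.** Accepting an HIV test is the behaviour that ZAIMARA is meant to change. Here, acceptance at the end of the first workshop day decides three things:

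- who can be found HIV-positive and exit;
- who has a documented negative baseline;
- who stays with unknown status.

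All three are determined after randomisation and after exposure to the assigned curriculum.

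For incidence, neither obvious analysis is clean. If girls untested on day 1 are kept, infections they already had cannot be told from new ones at the first later test. If the analysis is limited to day-1 negatives, it conditions on a choice made after randomisation.

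The problem reaches beyond HIV. The Background says most STIs are asymptomatic and that many go untreated. A girl tested on day 1 can be found infected and treated at the site clinic, whereas a decliner may carry the infection to a later visit, where it looks incident. Incident STI is tested formally as a binary secondary outcome, and the cost-effectiveness analyses are built on the three STIs.

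**Working it through.** **Inputs from the protocol.** HIV prevalence at age 15–19 is 3.3% (Background). HIV incidence is 2.54% per year, the testing proportion is 0.454, the detectable difference is 0.12 and there are 270 girls per arm after 10% attrition (Sample size). Each arm has 300–325 girls (Randomization).

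**Assumptions.** The protocol gives neither undiagnosed prevalence v at entry nor day-1 uptake u by arm. I take v from 1% to 3.3%, and u of 45.4% (HP) versus 57.4% or 90% (ZAIMARA). The 57.4% is the protocol's 6-month target, 0.454 + 0.12, borrowed for illustration; 90% is an upper scenario.

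**The plan's own figure.** With unpooled variance, n = (1.960 + 0.842)² × (0.454×0.546 + 0.574×0.426) / 0.12² = 269 per arm. Power at 270 is 80.2%. The sample size reproduces and is not in dispute.

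**Exits per 300 = 300 × v × u.**
- 45.4% versus 57.4%: 1.4 versus 1.7 at v = 1%; 4.5 versus 5.7 at v = 3.3%.
- 45.4% versus 90%: 1.4 versus 2.7 at v = 1%; 4.5 versus 8.9 at v = 3.3%.

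**Primary outcome under no effect, v = 3.3%, exits dropped.** Let e = v×u, and let t be the 6-month testing proportion that exiting girls would have had. The observed proportion is (0.454 − e×t)/(1 − e).
- 45.4% versus 57.4%: with t = 1, 0.4457 versus 0.4435 (−0.2 points); with t = 0, 0.4609 versus 0.4628 (+0.2 points).
- 45.4% versus 90%: −0.8 points (t = 1) to +0.7 points (t = 0).
- Power falls from 80.2% to 79.6% in the first scenario, and to 78.9% if all 3.3% exit from both arms.

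**Apparent 12-month HIV incidence with equal true incidence.** Untested girls are kept and all are tested later: [v(1 − u) + (1 − v)×0.0254] / (1 − v×u).

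| v | Day-1 uptake HP / ZAIMARA | HP | ZAIMARA | Ratio |
|---|---|---|---|---|
| 1% | 45.4% / 57.4% | 3.07% | 2.96% | 0.96 |
| 3.3% | 45.4% / 57.4% | 4.32% | 3.94% | 0.91 |
| 1% | 45.4% / 90% | 3.07% | 2.64% | 0.86 |
| 3.3% | 45.4% / 90% | 4.32% | 2.87% | 0.66 |
| either | 100% / 100% | 2.54% | 2.54% | 1.00 |

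**Prevalent share among girls untested on day 1.** Six-month incidence is 1 − exp(−0.0254×0.5) = 1.26%. The share of first positives at 6 months already present at entry is v/(v + (1 − v)×0.0126), which is 44% at v = 1% and 73% at v = 3.3%.

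**Effect of voluntary later testing.** Suppose later uptake is also 45.4% versus 57.4%, unrelated to infection or day-1 choice, and girls not tested later are kept as uninfected. Each ratio is then multiplied by 0.574/0.454 = 1.264: 0.91 becomes 1.15, and 0.66 becomes 0.84. The direction is therefore not fixed.

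**Restriction to day-1 negatives, v = 3.3%.** 300 × 0.454 × 0.967 = 132 in HP; 300 × 0.574 × 0.967 = 167 in ZAIMARA. The sets differ in size and, because acceptance follows exposure, possibly in composition.

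**STIs.** No figure can be given: the Background says STI prevalence is unknown. The mechanism is the same, except that STI-positive girls do not exit.

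**The case against.** The strongest reply is that little of this touches the main result, and that part stands. A reader might infer that the primary comparison is seriously biased or that intention-to-treat is abandoned. The documents support neither. The distortion is under 1 point in the scenarios tried. Leaving follow-up is not the same as leaving the analysis set, and the Missing data paragraph keeps the available data of non-completers and adds a sensitivity analysis for non-ignorable dropout.

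A reader might also infer that girls with a positive STI test exit. The exit rule names HIV only.

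A reader might take the HIV ratios as evidence of bias in ZAIMARA's favour. They depend on assumed uptake and on complete later testing, and with equal day-1 uptake the expected difference is zero. The protocol itself calls HIV incidence exploratory and underpowered, and HIV enters only the supplementary cost-effectiveness analyses. Limiting incidence to documented negatives is also an ordinary rule that an analysis plan may contain.

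That last reply does not dispose of the point. A rule restricted to negatives is sound when the test precedes randomisation. Here it would select on a post-randomisation choice, and analysis alone cannot fully repair that. Nor does the disclaimer about power extend to STI incidence.

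Finally, the Discussion describes on-site testing and PrEP as part of ZAIMARA's package, so moving the test might seem to change the intervention. But HIV testing is offered to girls in both arms, and the offer at the end of day 1 can remain.

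**Conclusion.** The point holds as a design weakness of modest severity that is cheap to correct. The order of procedures and the exit rule are stated outright for HIV; for the urine sample the order is only suggested. Exit and known-negative status may depend on arm, to the extent that day-1 acceptance does.

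The primary outcome is barely affected. What is exposed is STI incidence with its cost-effectiveness analyses, where the size cannot be computed from the document, and exploratory HIV incidence. For HIV, the apparent ratio under no true effect could lie between 0.66 and 0.96 in the scenarios above if all remaining girls are tested later, and could move towards or past 1 if they are not. These figures rest on the assumed undiagnosed prevalence and day-1 uptake.

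**What to change.** Within day 1, collect the baseline HIV and urine specimens after the survey and before randomisation. Leave result return, care, the PrEP offer and workshop attendance as planned. Define HIV and STI incidence among girls with a documented negative pre-randomisation test. Reconcile the Overview, Participants, Randomization and Study assessments paragraphs of Aim 2 with the Statistical analysis section, so that baseline means one thing throughout.

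The change uses the same visit and staff. It has two costs. Day-1 acceptance no longer reflects the workshop, but it is not a listed outcome. Some girls may decline before the workshop; the offer at the end of day 1 can still reach them, but they stay outside the documented-negative set, and any HIV exit among them needs the rule below.

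If the order cannot change:
- keep every randomised girl in the intention-to-treat denominator;
- treat HIV exits by one rule applied equally in both arms, with sensitivity analyses that count all of them as tested and none of them as tested. Crediting day-1 testing only to girls who exit would be asymmetric, because day-1 negatives get no such credit;
- report HIV and STI incidence under alternative assumptions about unknown baseline status.
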